#### Secondary Outcomes

The total number of health care telephone calls and emails (including specialist, family physician, and emergency department) related to the surgery will be captured at 4 weeks after surgery by the study coordinator over telephone (see Multimedia Appendix 3).

All complications will be recorded including infection, seroma, hematoma, and wound dehiscence. Among patients who receive tissue expanders, deflation is another possible complication. These complications will be collected via telephone survey at 4 weeks postoperative (see Multimedia Appendix 3).

Both mobile app and conventional follow-up patients at 4 weeks postoperative will complete our cost survey (Multimedia Appendix 4). The survey will collect data necessary to conduct cost estimates (presence of caregiver at time of follow-up, overnight hotel stays prior to clinic visit, etc).

For the purposes of this study, patients will receive a managed (loaner) mobile phone; however, a bring-your-own-device model is a more scalable solution and will be represented in the cost-effectiveness data [25].

In-person follow-up costs include foregone leisure time or income for the patient and foregone income for the caregiver, travel, and overnight hotel stay and parking costs associated with follow-up visits. Our cost survey (Multimedia Appendix 4) will collect information on caregiver presence at appointments, overnight hotel stays prior to appointments, total time commitment of in-person follow-up, and return to work information. In the literature, leisure time is often valued more than foregone income because subjects are choosing to forego their income for that leisure time. We will equally weight foregone income and leisure time, as patients are not choosing to be off work. They are off work because of a medical condition. We will determine foregone income based on average Ontario wages for a given age and sex of the patient. We will determine travel costs based on distance from home postal code to WCH.

Mobile phone follow-up costs include the foregone leisure time to submit follow-up data and the cost of data submission. We will determine foregone leisure time based on questionnaire time stamps from software records. Patient training sessions are held while patients are waiting for their preoperative appointment. There are no additional patient costs associated with this time.

In-person follow-up costs related to the health care system include the overhead (lighting, heating), physician fee, staffing costs including registrars, administrative assistance, nursing, and housekeeping. Two registrars service 32 clinic rooms. One administrative assistant and nurse is assigned to each breast reconstruction follow-up clinic. A follow-up clinic generally runs for 5 hours and serves 20 patients. WCH will provide hourly overhead and staffing costs, and OHIP billing codes will provide physician fees.

Mobile phone follow-up costs related to the health care system include the start-up costs of establishing assessment questionnaires for the patient populations to be monitored. This cost is based on the number of assessment questionnaires that need to be designed based on the diversity of the surgical population (eg, orthopedic versus general surgery patient monitoring). The QoC Health Inc mobile app can be loaded onto Android or iOS (Apple) smartphone or tablet. Formal training costs include the salary of the instructor from QoC Health Inc and the hourly salary of 1 administrative assistant, 1 postoperative ambulatory care unit nurse, and 2 physicians being trained. All staff turnover is >5 years; therefore, these costs will be amortized over 5 years. Current e-assessment OHIP physician billing codes are limited to dermatology and ophthalmology. There is no OHIP billing code for the postoperative or surgical e-assessment. The cost of software for the physician and patient and associated technical support is $3.50 (CAD) per patient per day [7]. There is discounting for hospitals based on how many patients are enrolled. Costs associated with patient training sessions include the administrative assistants’ hourly salary. The data required to send the smartphone assessment is equivalent to one email transmission.

Externally borne in-person follow-up costs include lost labor force once an individual has returned to work. In the cost survey (Multimedia Appendix 4), we will ask patients when they returned to work. We will add lost labor force costs to the in-person follow-up visits among patients who had returned to work using average Ontario wages based on the age and sex of the patient.

Patient satisfaction will be measured at 4 weeks after surgery using the post-pilot survey (Multimedia Appendix 1). The study coordinator will administer this over the telephone. The QoR-9 scores will be recorded at 4 weeks after surgery using the mobile app at home or a tablet during a scheduled clinic visit, depending on the patient’s study arm.

### Measuring Predictor Variables

Age impacts foregone wage estimates, and postal code impacts travel cost estimates. The type of surgical procedure, ASA classification, BMI, and preoperative radiation impacts rates of successful surgery at 30 days postoperative. Therefore, these variables are considered potential predictors of cost-effectiveness.

### Timeline

Any given patient may be recruited for the study up to 2 months prior to their surgery date. They will participate in the study for a total of 1 month following their surgery. Set-up and REB approval (1-2 months); a concurrent enrollment and data collection period to attain the required study participants (4-5 months); merging, cleaning, and debugging (1 month); and development of value messages for decision-makers and knowledge dissemination activities (2 months). This study will require approximately 1 year for completion. Its precise duration depends on the patient enrollment rate.

### Intervention Assignment Procedures

#### Randomization Strategy

All enrolled participants will be randomized to receive either the mobile app or conventional, in-person follow-up care in a ratio of 1:1 after giving informed consent for the study.

#### Sequence Generation

A block randomization scheme with variable block size will be generated using Stata ralloc [20]. This will ensure approximately equal sample size and that participants and study staff cannot anticipate assignment to either group. Treatments will be allocated in a 1:1 ratio. All study investigators and staff will be blinded to the block number, block size, and sequence in the block. The treatments will be assigned via pre-prepared sealed, opaque envelopes, and the envelopes will be ordered in the sequence of treatment assignments generated by the Stata code. Once eligibility for randomization has been determined, the first available allocation envelope will be assigned to the study subject. The subject will be randomized to the treatment arm indicated inside the envelope.

####  Allocation Concealment

As potential subjects are identified, a research assistant will be notified to assess eligibility. Once a subject is deemed eligible for enrollment, has given the necessary informed consent, has been enrolled, and has had her demographic information abstracted from her clinic records, the research assistant will issue the next in a series of sequentially numbered, sealed, opaque envelopes containing group assignment. The participant’s clinic number will be written on the envelope, and the participant will be required to open and read the treatment assignment in the presence of the research assistant, who will then enter the group assignment into a database and store the envelope. If a participant is unable to read, the research assistant will read the group assignment on her behalf.

####  Implementation of Randomization Procedures

A biostatistician (BZ) assigned to the study from the Institute of Health Policy, Management and Evaluation will carry out randomization procedures. The biostatistician will not be involved in any other aspects of conducting the study. The sequentially numbered, opaque, sealed envelopes containing group assignment will be given to the study coordinator. The study biostatistician will retain the key to treatment assignments. The study coordinator will be on site every day to ensure compliance with the study protocol.

## Results

### Data Analysis Plan

Descriptive statistics (frequencies, means, standard deviations) will be calculated for all clinical and outcome variables. All data obtained in this study will be entered into Excel and analyzed using Stata 13.

### Poisson Regression

We will use person-level Poisson regression to determine if there is a difference in the number of visits attended between patients in the mobile app and in-person follow-up arm.

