**Results:**

A sample of 72 (36 patients per group) will provide an E-test for count data with a power of 95% (*P*=.05) to detect a difference of 1 visit between groups, assuming a 10% drop out rate. Count variables will be analyzed using Poisson regression. Categorical variables will be tested using a chi-square test. Cost-effectiveness will be analyzed using net benefit regression. Outcomes will be assessed over the first 30 days following surgery.

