#### Why Use the QoC Health Inc Mobile App?

The QoC Health Inc mobile app allows patients to submit photos and answers to a validated quality of recovery (QoR) questionnaire and Visual Analog Scale (VAS) for the first 30 days postoperative using their mobile device [19]. A feasibility study, including 30 breast reconstruction patients, showed once daily reporting was well tolerated even in the first week postoperative period. There were high levels of satisfaction with the mobile device and app (3.9/5) and low levels of anxiety in knowing that their surgeon was monitoring their recovery [6]. One wound infection and one early dehiscence was picked up using the mobile phone app, leading to immediate intervention. Surgeons were able to follow patient reports on a Web portal. Post-pilot surveys reported an overall positive experience. All patients attended the standard in-person follow-up care visit at 1 and 4 weeks postoperative. Surgeons felt that at least one early follow-up clinic visit could be eliminated when using the remote monitoring technology. This was an unexpected finding [6].

The following proposed catalyst study builds on this pre-existing data by actually eliminating one or more in-person postoperative follow-ups and performs a cost-effectiveness assessment. Demonstrating cost-effectiveness in an elective ambulatory postoperative population would promote its use in similar surgical settings.

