### Sample Size

The average breast reconstruction patient attends two in-person follow-up visits within the first month after surgery. If we assume that we can avert at least one in-person visit in the mobile app arm and that we have equal number of participants in both groups, we can use the E-test for count data to generate a sample size of 64 (32 patients per group) at a power of 95% (*P*=.05). The E-test is more robust and more powerful than the Conditional test (C-test) originally described to compare two counts. If we assume a 10% dropout rate, we will increase our sample size target to 36 patients per group.

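### Poisson regression is fixed for all counts with no variance correction, although scheduled control visits and unplanned app-arm visits make variance equal to the mean unlikely, so the primary interval is likely to be miscalibrated

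*Protocol article*

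**What the plan says.** The Poisson Regression section gives the primary analysis: "We will use person-level Poisson regression to determine if there is a difference in the number of visits attended" by arm. The Results paragraph of the abstract sets the general rule: "Count variables will be analyzed using Poisson regression. Categorical variables will be tested using a chi-square test". Neither place names a variance estimator, a dispersion check or an exact method. Regression diagnostics appear only under Net Benefit Regression.

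On how visits arise, the article says three things:

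- Of the 30-patient pilot, under the heading on why the app is used: "All patients attended the standard in-person follow-up care visit at 1 and 4 weeks postoperative".
- Under Sample Size: "The average breast reconstruction patient attends two in-person follow-up visits within the first month after surgery". The effect is then set with "If we assume that we can avert at least one in-person visit in the mobile app arm", that is, 2 versus 1.
- Under Intervention, the control arm has one planned clinic visit, at 4 weeks, and the app arm has none at 1 or 4 weeks. App-arm visits arise from red flags or from the patient's own request (Intervention and Secondary Outcomes sections).

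The complication rate is given as 4% (Secondary Outcomes, Risks) and as about 5% (the section on ambulatory suitability). Nothing is said about how calls and emails are spread across patients.

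**The concern.** Ordinary Poisson regression takes the variance of each count to equal its mean and computes its standard error from that. A count produced by an appointment schedule that nearly everyone keeps varies much less than its mean. A count of unplanned visits may vary as a Poisson count does, or more if a few patients return several times. The two arms of this trial are built to differ in this way, so a single Poisson variance is unlikely to fit both.

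At stake is the width of the interval for the primary rate ratio, some power if only one control visit is planned, and the false-positive rate for calls and emails if contacts cluster in a few patients. Complications raise a related point: with so few expected events, one chi-square p-value can differ materially from an exact one.

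**Working it through.** **The plan's own figure.** With Poisson means 2 and 1, the normal approximation per arm is n = (z_α + z_β)² × (2 + 1) / 1². One-sided at 0.05 with 95% power this gives (1.645 + 1.645)² × 3 = 32.5. The exact E-test has 95.2% power at 32 per arm one-sided and 91.1% two-sided. Dropout: 32 / 0.9 = 35.6, so 36 per arm. The stated 32 and 36 reproduce, on a one-sided test and with variance equal to the mean in both arms.

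**Standard errors for visits.** With n per arm, means m and variances V (c = control, a = app):

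- model-based SE of the log rate ratio = √[1/(n·m_c) + 1/(n·m_a)]
- actual SE ≈ √[V_c/(n·m_c²) + V_a/(n·m_a²)]

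n = 32 is from Sample Size. Attendance, extra visits and the app-arm distributions are assumptions.

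A. Control: two scheduled visits at 95% attendance plus Poisson 0.1, so mean 2 and variance 2 × 0.95 × 0.05 + 0.1 = 0.195. App: Poisson, mean 1.
- Model: √(1/64 + 1/32) = 0.217
- Actual: √(0.195/128 + 1/32) = 0.181

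B. Same control. App: mean 0.3, variance 0.6.
- Model: √(1/64 + 1/9.6) = 0.346
- Actual: √(0.195/128 + 0.6/2.88) = 0.458

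C. One scheduled control visit at 95% attendance plus Poisson 0.3, so mean 1.25 and variance 0.0475 + 0.3 = 0.3475. App: Poisson, mean 0.65.
- Model: √(1/40 + 1/20.8) = 0.270
- Actual: √(0.3475/50 + 1/20.8) = 0.235

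Simulation, nominal 95% intervals and two-sided 5% tests:

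| Scenario | Coverage, model | Coverage, robust | Power, model | Power, robust |
|---|---|---|---|---|
| A | 98% | 94% | 97% | 99% |
| B | 88-89% | 92-93% | about 100% | about 100% |
| C | 98% | 94% | 74% | 86% |

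With full attendance in C (control exactly 1 plus Poisson 0.3, mean 1.3), power is 81% model-based and 91% robust.

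**Calls and emails.** If both arms share a variance/mean ratio r, the model-based SE is too small by √r, so the type I error is about 2 × [1 − Φ(1.96/√r)]: 5% at r = 1, 11% at 1.5, 17% at 2 and 26% at 3. Simulation with 32 per arm and means of 0.5 to 2 gives about 5%, 10%, 16% and 25%. Robust standard errors give about 5-8% over the same range. Every r here is an assumption.

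**Complications.** Expected events per arm run from 32 × 0.04 = 1.28 to 36 × 0.05 = 1.8, well under five. By exact enumeration over these sizes and rates, the chi-square test has size 2.2-3.8%, so it is not inflated. For 4/36 versus 0/36, though:

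- Chi-square = 72 × (4 × 36)² / (36 × 36 × 4 × 68) = 4.24, p = 0.040.
- Fisher: 2 × C(36,4)/C(72,4) = 2 × 58,905/1,028,790 = 0.115.

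**The case against.** The article does not say the standard errors are model-based. Poisson regression with a robust variance is still Poisson regression, and a condensed article may leave that choice to a fuller document. This stands to the extent that nobody can say the reported intervals will be wrong. It does not remove the point, because the article fixes the model while its own description of the visits argues against that model's default variance.

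The control count may also be less regular than the pilot suggests. Pilot patients were using the app, the trial outcome includes family physician and emergency visits, and the Intervention section plans one control visit where the pilot and Sample Size text imply two. That is fair: the amount of underdispersion is assumed.

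Underdispersion also errs on the safe side, and the primary test keeps its power at 2 versus 1. That stands for scenario A, but not for the interval in B or the power in C.

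Three stronger readings are tempting and are not supported:

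- A reader might put the app arm at close to exactly one visit each and find a standard error 2.5 times too large. The Intervention section gives that arm no planned visit at 1 or 4 weeks, so nothing holds its count near one.
- A reader might conclude that the calls and emails comparison will yield false positives. No dispersion figure supports that.
- A reader might take chi-square to be prescribed for the Likert satisfaction items. The abstract says only that it applies to categorical variables. It names neither satisfaction nor complications, though complications are presumably covered.

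**Conclusion.** The point holds in a limited form. Variance equal to the mean is unlikely for the primary outcome given how visits arise in each arm, and no correction is named. The direction of the error depends on the app arm: model-based intervals are too wide (98% coverage) if its visits are Poisson with mean 1, and too narrow (88-89%) if they cluster as in scenario B. The conclusion at the planned effect is safe, with about 97% power. Under a single planned control visit the loss is about 12 points of power (74% versus 86%).

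The calls and emails figures are conditional: 5% to 25% type I error over assumed ratios of 1 to 3. For complications the problem is sparse cells and fragile single p-values, with no excess of false positives overall. All visit results rest on 32 per arm and the stated distributions.

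**What to change.** Keep Poisson regression and the rate ratio, and state robust (sandwich) standard errors for all count outcomes: visits, calls and emails. In Stata, which the article already names, this is one option. It needs no new data and leaves the estimate unchanged. Coverage is then about 92-95% in the scenarios above. That is slightly short of nominal at this sample size, and the plan should say so.

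For complications, report the risk difference with a score or exact 95% confidence interval in place of reliance on chi-square. An exact test would not add power, since the limit is the number of events; the interval shows how little about three events in total can exclude.

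The Intervention section's control schedule and the two-visit figures in the pilot and Sample Size text must be reconciled, because the expected control count and its spread depend on them. The cost is a change of wording before analysis.

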### Net Benefit Regression

We will perform a person-level net benefit regression to determine the cost-effectiveness of this intervention. We will define cost as all societal costs incurred over the 30 days after surgery. We will define effect as the rate of complication over the 30 days after surgery. We will regress net benefit (dependent variable) on study arm, age, distance from home to hospital (km), BMI, BMI^2^, ASA classification, radiation status, and major or minor procedure (independent variables). Net benefit, age, distance, BMI, and BMI^2^ are continuous variables. ASA classification is a categorical variable. Study arm, radiation status, and major or minor procedure are binary variables (1=mobile app; 0=in-person and 1=yes, 0=no), where:

nb = B0 + B1(TX) + B2(age) + B3(km) + B4(BMI) + B5(BMI^2^) + B6(ASA) + B7(radiation) + B8(major/minor)

We will perform regression diagnostics and use these diagnostics to advise on the use of parametric versus non-parametric generation of 95% confidence intervals. We will use our net benefit regression to generate an incremental net benefit (INB):

INB = WTP * (effect_i_ – effect_c_) – (cost_i_ – cost_c_), where:

effect_i_ = mean effect of the intervention, ie, rate of complication in the mobile app arm at 30 days

effect_c_ = mean effect of the control, ie, rate of complication in the in-person arm at 30 days

cost_i_ = mean cost of the intervention, ie, societal costs from baseline to 30 days

cost_c_ = mean cost of the control, ie, societal costs from baseline to 30 days

In this situation, where willingness to pay is unknown, we assigned numerous values for willingness to pay and generated a cost-effectiveness acceptability curve (CEAC) based on these theoretical values [26]. The CEAC illustrates the probability that the intervention is cost-effective by graphing the probability that B1>0 as a function of willingness to pay (WTP) [27].

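### Net benefit takes the complication rate as its effect with a plus sign, so extra complications in the app arm raise the app's apparent cost-effectiveness

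*Protocol article*

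**What the plan says.** Everything needed is in the Net Benefit Regression section of the protocol article.

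- The effect is a harm: "We will define effect as the rate of complication over the 30 days after surgery". The arm-level definitions repeat this: "effect_i_ = mean effect of the intervention, ie, rate of complication in the mobile app arm at 30 days" and "effect_c_ = mean effect of the control, ie, rate of complication in the in-person arm at 30 days".
- The formula adds that effect with a positive multiplier: "INB = WTP * (effect_i_ – effect_c_) – (cost_i_ – cost_c_), where".
- Study arm is among the "binary variables (1=mobile app; 0=in-person and 1=yes, 0=no", so the arm coefficient B1 is the incremental net benefit of the app.
- The acceptability curve is drawn by "graphing the probability that B1>0 as a function of willingness to pay (WTP"), and its height is read as the probability that the app is cost-effective.
- WTP is not fixed: "where willingness to pay is unknown, we assigned numerous values for willingness to pay".

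The section does not reverse-code the effect, express it as complications avoided, or give WTP a negative sign.

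**The concern.** Incremental net benefit puts a money value on health gained and subtracts the extra cost. It works only if a larger effect is a better outcome. The complications listed under Measuring Outcome Variables are infection, seroma, hematoma, wound dehiscence and expander deflation, so a larger value here is worse.

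An analyst who follows the text literally would find the app more cost-effective if it raised complications and less so if it lowered them. The distortion grows with WTP. Costs are a named secondary outcome, and the Knowledge Translation Plan makes demonstrated cost-effectiveness the ground for extending the app to other surgical divisions. The Risks section also accepts that app follow-up may change when a complication is diagnosed. Complications are therefore the harm that this analysis most needs to carry with the right sign.

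**Working it through.** The protocol gives no numerical net benefit or acceptability value, so there is no figure to reproduce. The check is algebra, followed by an illustration.

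**Inputs from the protocol article**
- Effect, formula, arm coding and decision rule: Net Benefit Regression, as quoted.
- Background complication rate 4%: Secondary Outcomes.
- 36 patients per group: Sample Size.
- Software charge CAD 3.50 per patient per day: Measuring Outcome Variables.

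**Assumptions not in the protocol**
- App complication rate of 8% or 2%.
- WTP values of CAD 0 to 50,000 per complication.
- Cost difference (app minus in-person) of −100 or +100.
- Cost SD of 200 in each arm.
- Cost and effect independent.

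**Algebra.** Let p_i and p_c be the complication rates on the app and in person, and ΔC the cost difference.

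- As written: INB = WTP × (p_i − p_c) − ΔC
- Correctly signed: INB = WTP × (p_c − p_i) − ΔC
- Written minus correct: 2 × WTP × (p_i − p_c)

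The derivative of the written INB with respect to p_i is +WTP, so it rises with every app complication. The person-level dependent variable is not printed. For B1 to reproduce the stated INB, it has to be WTP × complication − cost, which credits WTP to each patient who has a complication.

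**Size of the effect term alone, 8% against 4%**
- WTP 1,000: 1,000 × 0.04 = +40 as written, −40 correct.
- WTP 10,000: +400 as written, −400 correct, an error of 800.
- WTP 50,000: +2,000 as written, −2,000 correct, an error of 4,000.

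A smaller case is one extra event among 36, which is 1/36 = 2.8 percentage points. At WTP 10,000 this gives +278 as written instead of −278, an error of about CAD 556 per patient.

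For scale, the software charge is 3.50 × 28 = CAD 98 over the four weeks of reporting in the Abstract. Over the 14 + 28 = 42 days implied by the Intervention section it is 3.50 × 42 = CAD 147. Travel, wage and clinic costs also enter ΔC, so this is a reference point only.

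**INB with ΔC = −100 (CAD per patient)**

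| WTP | 8% vs 4%, written | 8% vs 4%, correct | 2% vs 4%, written | 2% vs 4%, correct |
|---|---|---|---|---|
| 0 | 100 | 100 | 100 | 100 |
| 1,000 | 140 | 60 | 80 | 120 |
| 5,000 | 300 | −100 | 0 | 200 |
| 10,000 | 500 | −300 | −100 | 300 |
| 20,000 | 900 | −700 | −300 | 500 |

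**Acceptability curve.** P(B1>0) = Φ(INB/SE), with SE² = WTP² × [p_i(1−p_i) + p_c(1−p_c)]/36 + 2 × 200²/36.

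For 8% against 4% at WTP 10,000, SE² = 10,000² × 0.112/36 + 2,222 ≈ 313,333, so SE ≈ 560. With ΔC = −100:
- Written: Φ(500/560) = 0.81.
- Correct: Φ(−300/560) = 0.30.

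All four cases at WTP 10,000:

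| ΔC | App rate vs 4% | Written | Correct |
|---|---|---|---|
| −100 | 8% | 0.81 | 0.30 |
| −100 | 2% | 0.40 | 0.77 |
| +100 | 8% | 0.70 | 0.19 |
| +100 | 2% | 0.23 | 0.60 |

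As WTP grows the cost term becomes negligible and the written curve tends to P(p_i > p_c). For 8% against 4% at WTP 50,000 it stands at 0.77 (ΔC = −100) or 0.75 (ΔC = +100). The correctly signed values are 0.25 and 0.23.

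**The case against.** The best defence is that this is a slip of wording. Measuring Predictor Variables speaks of rates of successful surgery at 30 days, which suggests that a favourable outcome was in mind, and the person-level net benefit is never written out. An analyst who knows the method might correct the sign without comment. But the section that governs the analysis names the complication rate three times and pairs it with an explicit formula, arm coding and decision rule. The favourable outcome is not carried into any of these. This is a stated rule that gives the wrong sign, not a detail left to a fuller document.

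Several limits do stand:
- Only the effect term is reversed. At WTP = 0, or with equal complication rates, the point INB is the same under either sign.
- The 8% rate and the WTP values are illustrative, and the curve heights also depend on the assumed cost SD and on independence of cost and effect. The direction of the error depends on none of these.
- The analysis is secondary. The Poisson comparison of visits and the separate reporting of complications are unaffected.

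The low complication rate does not make the error harmless. With about 36 patients per arm, a chance difference of one or two events is plausible, and WTP multiplies it.

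**Conclusion.** The concern holds. Followed as written, the plan gives a cost-effectiveness result whose effect part has the wrong sign whenever WTP is above zero and the complication rates differ. The error is exactly 2 × WTP × (p_i − p_c). At an assumed WTP of CAD 10,000 that is about CAD 556 per patient for a one-patient difference in arms of 36, and CAD 800 for 8% against 4%. In the illustrations this moves the probability of cost-effectiveness across one half in both directions. The sign of the error follows from the protocol's own definitions; only the amounts rest on assumed values. It should be corrected before any economic analysis is run.

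**What to change.** Define effect as complication-free at 30 days (1 = no complication, 0 = any) and keep the formula. Then effect_i − effect_c = (1 − p_i) − (1 − p_c) = p_c − p_i, which has the right sign. Equivalently, keep the complication rate and write INB = WTP × (complication_c − complication_i) − (cost_i − cost_c).

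In either case:
- Write out the person-level dependent variable: nb = WTP × complication-free − cost.
- Label WTP as willingness to pay per complication avoided.
- Use the same coding in the regression, the INB and the acceptability curve, so that B1 > 0 favours the app.

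The cost is one line of the analysis plan and one recode. No extra data or patients are needed, and the primary analysis does not change.
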